### Sample size

We aim to recruit 720 patients into this feasibility study. This is based on the following assumptions:Average length of stay of 14 days and 25-bed wards will provide a recruitment pool of 4800 patients over the course of 6 months.Fifty percent of patients are assumed to be at risk of delirium, giving 2400 eligible patients.On the basis of previous studies of comparable populations [58, 59], 30 % of patients will consent.

Because this is a feasibility study, a formal power calculation is not appropriate, as effectiveness is not being evaluated. The results generated from this study will be used to inform the power calculation for a possible definitive study.

### Analysis

Statistical analysis is the responsibility of the University of Leeds CTRU statistician, and a final statistical analysis plan will be written before any analysis is undertaken. All analyses and data summaries will be conducted on the intention-to-treat (ITT) population, defined as all participants registered, regardless of non-compliance with the protocol or withdrawal from the study. No formal interim analyses are planned, and final analysis will take place when all available data have been received. The analysis will be focused on descriptive statistics and confidence interval estimation rather than on formal hypothesis testing.

#### Primary analysis

##### Estimation of effectiveness for a possible definitive randomised controlled trial

To inform the sample size calculation for a possible definitive trial, we will calculate the incidence of new-onset delirium within 10 days of admission by ward type, overall and per arm, together with corresponding 95 % confidence intervals. Estimation of effectiveness will be carried out on the ITT population using multilevel logistic regression adjusting for NICE risk factors for delirium, medications which could impact on the development of delirium, hearing impairment and use of hearing aid, visual impairment and ward type. Ward type will be fitted as a random effect in the model. Odds ratios, 95 % confidence intervals and *p* values will be reported. The number of new patients admitted per ward during the recruitment period will be used to estimate cluster size. The intracluster correlation coefficient will be calculated using the incidence of new-onset delirium expressed as a proportion.

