**Methods/Design:**

The Prevention of Delirium Study is a multicentre, cluster randomised feasibility study designed to explore the potential effectiveness and cost-effectiveness of the Prevention of Delirium Programme. Sixteen elderly care medicine and orthopaedic/trauma wards in eight National Health Service acute hospitals will be randomised to receive the Prevention of Delirium Programme or usual care. Patients will be eligible for the trial if they have been admitted to a participating ward and are aged 65 years or over. The primary objectives of the study are to provide a preliminary estimate of the effectiveness of the Prevention of Delirium Programme as measured by the incidence of new onset delirium, assess the variability of the incidence of new-onset delirium, estimate the intracluster correlation coefficient and likely cluster size, assess barriers to the delivery of the Prevention of Delirium Programme system of care, assess compliance with the Prevention of Delirium Programme system of care, estimate recruitment and follow-up rates, assess the degree of contamination due to between-ward staff movements, and investigate differences in financial costs and benefits between the Prevention of Delirium Programme system of care and standard practice. Secondary objectives are to investigate differences in the number, severity and length of delirium episodes (including persistent delirium); length of stay in hospital; in-hospital mortality; destination at discharge; health-related quality of life and health resource use; physical and social independence; anxiety and depression; and patient experience.

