### Unit of randomisation

Cluster randomisation has been chosen to reduce between-group contamination, as the POD system of care is a ward-based intervention which aims to affect staff skills, knowledge and clinical practice. As patients on a ward receive the allocated treatment, it is not possible to use the patient as the unit of randomisation. It is not known whether treatment contamination might occur between wards owing to staff movement, and therefore this will be investigated by randomising half of the hospitals at the hospital level (control or intervention) and half of the hospitals at the ward level. Randomisation will stratify by ward type (geriatric medicine and orthopaedic trauma) and is a two-stage process which will be performed centrally by the statistician at the Clinical Trials Research Unit (CTRU). Sites will first be randomised 1:1 between site- (i.e., hospital)-level allocation (both wards in the hospital receive the same intervention) and ward-level allocation (each ward in the hospital receives a different intervention). Those sites selected for site-level allocation will then be further randomised 1:1 for both of their wards to receive either POD or control. Wards in those sites selected for ward-level allocation will be randomised 1:1 to receive either POD or control (Fig. 1).

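### The effectiveness model names ward type, a two-level stratification factor, as its random effect and names no ward or hospital effect, so the interval for the preliminary odds ratio would be too narrow

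*Protocol article*

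**What the plan says.** In the protocol article, Primary analysis, the subsection on estimation of effectiveness sets out the model: "Estimation of effectiveness will be carried out on the ITT population using multilevel logistic regression". The adjustment list ends with "hearing impairment and use of hearing aid, visual impairment and ward type". The next sentence reads "Ward type will be fitted as a random effect in the model". Odds ratios, 95% confidence intervals and p values are to be reported from this model. The subsection names no random effect for ward or for hospital.

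The allocation is described under Unit of randomisation and in the abstract:

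- Number of units: "Sixteen elderly care medicine and orthopaedic/trauma wards in eight National Health Service acute hospitals will be randomised".
- Level of allocation: "randomising half of the hospitals at the hospital level (control or intervention) and half of the hospitals at the ward level".
- Ward-level sites: "Wards in those sites selected for ward-level allocation will be randomised 1:1 to receive either POD or control".
- Role of ward type: "Randomisation will stratify by ward type (geriatric medicine and orthopaedic trauma").

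The Analysis section puts the emphasis on "descriptive statistics and confidence interval estimation rather than on formal hypothesis testing". The preliminary estimate of effectiveness is the first primary objective under Aims and objectives.

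**The concern.** A random effect in a cluster trial should represent the units that carry the correlation. Here those are the wards and, where allocation is by site, the hospitals. Ward type is neither. It has two fixed categories of direct interest, and a variance estimated from two levels rests on 1 degree of freedom. It is also listed among the covariates. If it is fitted both ways, the fixed effect absorbs the difference between the two types, nothing is left for the random effect, and the model is in effect an ordinary logistic regression.

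Either way, correlation between patients on the same ward is left out. The protocol itself expects such correlation: it randomises by cluster and makes the ICC a primary objective. At stake is the precision claimed for the preliminary odds ratio, in an analysis whose stated emphasis is interval estimation and whose stated use is planning a definitive trial.

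**Working it through.** **Inputs from the protocol.** The Sample size section gives a pool of 4800, 50% at risk and 30% consenting: 4800 × 0.50 × 0.30 = 720, which reproduces the target. With 16 wards, the average cluster is 720/16 = 45.

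**Inputs assumed.** The documents give no ICC, because estimating it is an objective, and no planning incidence. I take ICCs of 0.01, 0.02 and 0.05 for patients on the same ward after adjustment, equal ward sizes, and 15% incidence where a simulation needs one.

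**Design effect.** DE = 1 + (45 − 1) × ICC. An interval that ignores ward has a standard error too small by a factor √DE, so its actual error rate is 2 × [1 − Φ(1.96/√DE)].

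| Assumed ICC | DE | √DE | Effective N (720/DE) | Actual error | Actual coverage |
|---|---|---|---|---|---|
| 0.01 | 1.44 | 1.20 | 500 | 10.2% | 90% |
| 0.02 | 1.88 | 1.37 | 383 | 15.3% | 85% |
| 0.05 | 3.20 | 1.79 | 225 | 27.3% | 73% |

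**Does the mixed allocation upset this?** Not for the simple contrast with 8 wards per arm. A shared hospital effect counts twice in the 4 hospital-level sites (4 × 2² = 16) and cancels in the 4 ward-level sites (0). The total of 16 is the same as for 16 independent wards (16 × 1²). The ward-level formula is therefore a fair approximation, with the ICC taken as the total correlation within a ward.

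**Check on the stated model itself.** A null simulation used 800 trials per setting, 8 hospitals with one ward of each type, 45 patients per ward, 15% incidence and 30% of the cluster variance at hospital level. It fitted a random intercept for ward type, and compared it with a random intercept for ward plus fixed ward type. ICCs are on the latent logistic scale.

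| Latent ICC | Ward-type model rejects | Ward model, z limits | Ward model, t on 13 df |
|---|---|---|---|
| 0 | 4.4% | 4.4% | 2.4% |
| 0.02 | 10.7% | 8.3% | 5.4% |
| 0.05 | 19.3% | 10.4% | 7.5% |

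At latent ICC 0.05 the ward-type model reported a mean standard error of 0.208 against an actual standard deviation of 0.310 for the log odds ratio. The ward model gave 0.279 against 0.325.

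**Why the two tables differ.** The scales differ. A latent ICC of 0.05 is a variance of (0.05/0.95) × π²/3 = 0.173. Multiplied by 0.15 × 0.85 = 0.1275, this is roughly 0.022 on the proportion scale, so its 19.3% belongs beside the 15.3% row of the first table and not the 27.3% row. The direction is the same in both, and with no clustering the stated model behaves correctly.

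**The case against.** The best defence is that the sentence is a slip. The model is called multilevel, ward type already stands in the covariate list, and the next sentence but one counts cluster size per ward. An author who meant ward could easily have written this. That is plausible, and it is why one should not assert that the trial team overlooked clustering. But no ward level is stated anywhere in the subsection. The article does not leave the random structure to the analysis plan: it fixes it, on the wrong factor. A slip needs the same correction.

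Three stronger readings are tempting and are not supported.

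- *The study would obtain the wrong ICC.* The same subsection calculates the ICC separately, from the incidence expressed as a proportion, and does not take it from this model.
- *A null programme could be carried forward on a false positive.* The continuation criteria rest on wards completing the milestone checklist and on the recruitment rate. The Sample size section says that effectiveness is not being evaluated. No stated decision depends on this interval or p value.
- *Reporting p values contradicts the Analysis section.* That section says where the emphasis lies; it does not exclude p values. Whether to print them is a matter of preference.

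It is also fair to say that the size of the effect depends on ICCs that the documents do not give.

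**Conclusion.** The sentence is wrong as written. The stated random effect is not a randomised unit, and a literal fit leaves the clustering out of the interval for the first primary objective. The direction holds for any positive ICC. The size is illustrative: coverage of about 90%, 85% and 73% at assumed ICCs of 0.01, 0.02 and 0.05, with 45 patients in every ward. The damage is limited to an overprecise preliminary odds ratio, which could narrow the range of effects considered plausible when the definitive trial is planned. It does not extend to the ICC estimate or to the progression decision.

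**What to change.** Replace the sentence so that ward (16 levels) is the random intercept, with arm and ward type as fixed effects. State that limits use a small-sample correction with between-cluster degrees of freedom, or add a ward-level summary analysis as a check. The correction matters: with ordinary z limits the ward model still rejected 8.3% and 10.4% in the simulation.

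Allow for hospital as well, since it is the allocated unit in half of the sites. With only 8 hospitals of two wards each its variance will be poorly estimated, so a sensitivity analysis is a reasonable minimum. The ward-within-hospital model was not simulated here, and the ward-only model with t limits was still somewhat above nominal (7.5%) at the largest ICC tried.

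The cost is a wider interval. Using t on 13 df (2.16), the ratio to the interval ignoring ward is √DE × 2.16/1.96, or about 1.3, 1.5 and 2.0 at the three assumed ICCs. No new data are needed. The Trial status section says that analysis is under way, so any fit already made with ward type as the random effect should be rerun before it is reported.

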##### Assessment of intervention delivery and compliance

The progress of wards randomised to POD will be assessed by completion of the internal milestone checklist, which includes the length of time taken to complete each core task (staff education, review of current practice and ward systems) and overall time spent implementing POD, the number of sites and/or wards failing to progress through implementation milestones and reasons for failure, the number of sites and/or wards withdrawing during the implementation and delivery phases, the number of sites withdrawing from the study, timing and reason for withdrawal, case notes review and review of ward observation of care.

##### Estimation of recruitment uptake

To assess the feasibility of recruiting participants, the numbers of patients who are screened, are eligible, are assessed for delirium, have prevalent delirium, have capacity to consent, consent to trial registration and are registered will be summarised. Loss to follow-up at 30 days and 3 months, as well as the number, timing and reasons for withdrawals, will also be reported.

##### Assessment of the degree of contamination

The number of staff moving between study wards within sites will be reported. The incidence rates of new-onset delirium at the sites that were randomised at the hospital level will be calculated and compared with those from sites that were randomised at the ward level to assess the degree of contamination between wards.

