### Intervention

POD is a manualised, multicomponent intervention and systematic implementation process designed to secure ward practice changes, potentially enhanced by the involvement of hospital volunteers. It builds on current best evidence on delirium prevention [3], conceptually driven empirical research [48] and reviews of implementation [29, 49, 50].

The POD intervention comprises actions centred on 10 targeted risk factors associated with the development of delirium among those who are vulnerable on of the basis of predisposing risk [3]. These interventions directly affect the patient experience of care and include optimising hydration and nutrition, reducing environmental threats (excessive noise, multiple moves), increasing orientation to time and place, improving communicative practices (personally meaningful interaction and cognitive stimulation), supporting and/or encouraging mobility and better management of pain and infection. The implementation process is supported and reinforced through raising awareness and training of staff and volunteers in delirium prevention. Alongside this, staff will be involved in an action-planning cycle of observation and audit of current practice to establish what needs to be put in place to introduce the POD system of care. The principles underpinning POD and the steps in the change process to facilitate action on the intervention are standard and generalisable, although the specific systems or mechanisms are flexible, depending on preexisting practice and local decision-making.

Wards randomised to the POD system of care will undergo a 6-month implementation period to allow the intervention to be embedded into ward practice before patient recruitment. Local implementation teams, including a study-specific ward nurse, will be convened, and training will be provided in the implementation and delivery of the POD system of care by the central trial team. Progress on implementation will be monitored by the central trial team through regular site visits and telephone and/or email contact and will be tracked through completion of an internal milestone checklist embedded within the POD manual.

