### Usual-care control group

Wards randomised to the usual-care control group will continue to deliver care as determined by local policies and practices.

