Compliance with the POD system of care will be assessed by the central trial team through review of site-specific POD documentation, case note review and researcher-conducted observations of ward care using the method employed in the 2013 National Audit of Dementia Care in General Hospitals [57]. Sustainability will be assessed through observations of ward care approximately 3–6 months post recruitment through central trial team researcher-conducted observations of ward care. Information will be collected on intervention delivery, recruitment uptake, follow-up rates, missing data, length of hospital stay, staff movement (to allow for an assessment of potential contamination), the number of falls between consent and discharge, and deaths occurring up to 3 months post admission. We will also collect related and unexpected serious adverse events.

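### The staff-movement count for contamination has no direction and includes sites where it cannot occur, and no analysis of POD-type care on control wards is stated

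*Protocol article*

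**What the plan says.** All references are to the protocol article.

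- **Aims and objectives** lists the degree of ward-level contamination from staff moving between wards as a primary objective.
- **Unit of randomisation** builds the design around this. Half of the eight hospitals are randomised as a whole, so both wards get the same allocation. The other half are randomised by ward, so the two wards get different allocations.
- **Assessment of the degree of contamination** fixes two measures. The first is a count: "The number of staff moving between study wards within sites will be reported". The second takes delirium incidence at sites randomised by hospital, to be "compared with those from sites that were randomised at the ward level to assess the degree of contamination between wards".
- **Assessment of intervention delivery and compliance** opens with POD wards: "The progress of wards randomised to POD will be assessed by completion of the internal milestone checklist". The same sentence ends its list with "case notes review and review of ward observation of care".
- **Data collection** says compliance with POD will be assessed through "review of site-specific POD documentation, case note review and researcher-conducted observations of ward care", without naming the arm. It also lists staff movement as an item collected in order to assess contamination.
- **Usual-care control group** says only that control wards "will continue to deliver care as determined by local policies and practices".
- **Intervention** says that implementation is supported by "raising awareness and training of staff and volunteers in delirium prevention", so the people who carry POD skills may include volunteers.

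**The concern.** Contamination here means that control patients receive POD-type care because people trained in POD work on their ward. A count of moves between the two study wards of a hospital is at best a loose proxy for that. A high count could consist entirely of moves between wards in the same arm. A low count could coexist with real exposure if a few trained people spend much of their time on the control ward, because the count as stated carries no duration.

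The trial has to inform whether a definitive trial should randomise wards or hospitals. If the difference between arms is small, an ineffective programme, leakage to control wards and usual care that already resembles POD are all possible explanations. Telling them apart needs some view of the care given on control wards, and no stated analysis provides one.

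**Working it through.** **1. Which moves can contaminate.** Inputs from Setting and Unit of randomisation: 8 hospitals, 16 wards, 1:1 at each stage.

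- Hospital-level sites: 4, of which 2 are all POD and 2 all control. That gives 4 POD and 4 control wards, and no move between a site's two wards crosses arms.
- Ward-level sites: 4, each with one POD and one control ward. That gives 4 POD and 4 control wards.
- Total POD wards: 8. This agrees with the progression criterion, where six wards are 75 %: 6 / 0.75 = 8.

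Let w be the share of counted moves that occur at ward-level sites, and d the share of those that go from POD to control. The share that can contaminate is w × d. With equal movement everywhere, w = 4/8 and d = 1/2, so w × d = 1/4. The article gives neither w nor d, so the share could lie anywhere from 0 to 1, and the count as stated would not reveal it.

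**2. Whether the incidence comparison fills the gap.** The article gives no precision for it, so this is an illustration.

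Patients per ward: the Sample size section reproduces as 16 × 25 × (168/14) = 4800, and 4800 × 0.50 × 0.30 = 720. Then m = 720/16 = 45.

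Assumptions: control incidence p of 10 to 30 %; full POD effect equal to the odds ratio of 0.47 quoted in Background; intracluster correlation (ICC) of 0.01 to 0.05; 50 % of the POD effect leaking to control wards at ward-level sites.

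- POD incidence: p₁ = o/(1 + o), with o = 0.47 × p/(1 − p).
- Shift, control wards only: 0.5 × (p − p₁). Both arms pooled: half of that.
- Design effect: D = 1 + 44 × ICC, which is 1.44 or 3.2.
- Half-width, control wards only: 1.96 × √[2p(1 − p)D/180], with 4 × 45 = 180 patients per group.
- Half-width, pooled: the same form with the mean of p and p₁ in place of p, and 8 × 45 = 360 per group.

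Example with p = 10 %, ICC 0.01: 1.96 × √(2 × 0.09 × 1.44/180) = 7.4 points.

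| p | p₁ | Shift, control only | Half-width (ICC 0.01 to 0.05) | Shift, pooled | Half-width (ICC 0.01 to 0.05) |
|---|---|---|---|---|---|
| 10 % | 5.0 % | 2.5 | 7.4 to 11.1 | 1.3 | 4.6 to 6.9 |
| 20 % | 10.5 % | 4.7 | 9.9 to 14.8 | 2.4 | 6.3 to 9.4 |
| 30 % | 16.8 % | 6.6 | 11.4 to 16.9 | 3.3 | 7.4 to 11.1 |

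Shifts and half-widths are in percentage points. No shift reaches its half-width. Even with 100 % leakage, only one case does: control wards only, p = 30 %, ICC 0.01, with 13.2 against 11.4. The half-widths are also favourable, because they ignore clustering within hospitals: the four control wards at hospital-level sites come from only two hospitals.

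**3. Control-ward care.** Set side by side, the delivery section is worded for POD wards, the data collection section leaves the arm open but speaks of compliance with POD, and the control-group section describes no monitoring. No section states an analysis of POD-type care on control wards.

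**The case against.** The strongest reply is that the count is only supporting description, and that the incidence comparison by level of randomisation is the assessment the design was built for. That is fair as a reading of the design, and contamination does not rest on the count alone. But the comparison is based on outcome, is not limited to control wards, and on the assumptions above is too imprecise to carry the objective.

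A second reply is that a condensed article may leave direction, staff roles and tabulation by allocation to the full protocol or analysis plan. This stands in part: nothing says that direction will not be recorded. The article does, however, state what will be reported for a primary objective, and that quantity is not contamination.

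Three stronger readings are tempting and are not supported:

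- A reader might infer that care is observed only on POD wards. The Data collection section does not restrict case note review or ward observation by arm, so control-ward data are unstated, not excluded.
- A reader might infer that control wards are free to take up their own delirium programmes. The ward exclusion criteria bar wards that intend such an initiative during the study. This lowers the risk but does not measure usual care.
- A reader might infer that therapists, doctors or volunteers routinely serve both wards unseen by the count. The article does not say so, and volunteers are an optional component.

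**Conclusion.** The point holds in limited form. As stated, the staff count does not measure contamination, because it mixes moves that cannot cross arms with moves that can and does not separate POD-to-control from the reverse. The incidence comparison does not make up for this, and no analysis of POD-type care on control wards is stated.

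The size of the mixing is unknown. The 1-in-4 figure rests on equal movement across sites and directions and should not be read as an estimate. The imprecision result rests on assumed control incidence, ICC and leakage, and on borrowing the odds ratio of 0.47 as the POD effect. No figure in the article is wrong on this point.

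**What to change.** 1. For the four ward-level sites, report the number of POD-trained staff, and volunteers where used, who worked on the control ward during recruitment. Show moves at hospital-level sites separately, as background.
2. Limit the incidence comparison to control wards, ward-level against hospital-level sites, and give a confidence interval.
3. Report the case note review and ward observation for both arms, by level of randomisation.

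The first item draws on staff-movement data that the article already plans to collect, provided those records identify direction and training. The second is a change of tabulation. The third costs some central-team time for control-ward notes and observation if these were not already planned. Trial status reports recruitment closed and analysis under way, so observations not made during recruitment cannot be recovered, whereas case notes could still be reviewed where they are available. No additional patients are needed.

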### Setting

#### Ward inclusion criteria

The study will be conducted in eight NHS hospitals (16 wards) which care for those at risk of developing delirium (geriatric medicine or orthopaedic trauma wards). The following ward criteria were identified in the preliminary study and were applied to maximise the likelihood of successful implementation of the POD system of care:Involvement of senior nurse, ward manager and voluntary services manager (if voluntary services were selected by local staff as a component of the intervention)Named person responsible for supporting the implementation of POD (e.g., a senior nurse)Dedicated time (equivalent to 1 day per week) of an experienced senior nurse to lead the implementation period (funded with the research grant)Adequate staffing levels as assessed in reference to guidance on nurse staffing [41, 42]

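### The contamination assessment compares delirium incidence between hospital-level and ward-level sites without naming an arm; read as written it averages POD with control and does not identify contamination

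*Protocol article*

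**What the plan says.** Assessing ward-level contamination from staff movement is one of the primary objectives (Aims and objectives). It is also the stated reason for the two-level design (Unit of randomisation): "this will be investigated by randomising half of the hospitals at the hospital level (control or intervention) and half of the hospitals at the ward", that is, with the ward as the unit in the second half.

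The same section fixes the arm mix. "Sites will first be randomised 1:1 between site- (i.e., hospital)-level allocation" and ward-level allocation. For the first type, "Those sites selected for site-level allocation will then be further randomised 1:1 for both of their wards to receive either POD or control". In the second type the two wards of a hospital receive different interventions. With eight hospitals and 16 wards (Ward inclusion criteria), this gives about four hospitals of each type and about four POD and four control wards within each type.

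The section Assessment of the degree of contamination plans two things. First, "The number of staff moving between study wards within sites will be reported". Second, delirium incidence at the hospital-level sites "will be calculated and compared with those from sites that were randomised at the ward level to assess the degree of contamination between wards". The unit of that comparison is the site, and no arm is mentioned. Elsewhere the article names the arm where it wants one: the Primary analysis section asks for incidence overall and per arm, and the Secondary outcomes section asks for deaths, eligibility violations and falls overall and by arm. The regression model in the Primary analysis section lists no term for level of randomisation and no arm-by-level term.

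**The concern.** Contamination in a split hospital makes its two wards more alike: control wards may pick up POD practice, POD wards may slip towards usual care, or both. The signal is therefore a narrower gap between arms at ward-level sites than at hospital-level sites. A comparison of overall incidence by site type does not look at that gap. It looks at the average of the two arms, which contamination may lower, raise or leave unchanged.

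The study exists to inform a definitive trial, in which the choice between randomising wards and randomising hospitals is central. A result near zero could be read as reassurance when the arms had converged. A non-zero result could come from contamination in either direction, or simply from one group of hospitals having a higher underlying incidence.

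**Working it through.** **Inputs from the article.** Eight hospitals, 16 wards, 1:1 at each randomisation step; odds ratio 0.47 for multicomponent interventions and an occurrence of 29–64% on general medical and old age medicine wards (Background); target 720 patients (Sample size).

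**Assumptions.** Equal ward sizes. Control incidence is not a planning figure in the article; 29%, the lower end of the quoted range, is used for illustration and varied below. No intracluster correlation (ICC) is given; 0 to 0.05 is used.

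**The plan's own figure.** The article gives none for this contrast. The recruitment target reproduces: 16 × 25 × (168/14) = 4800, taking 6 months as 24 weeks; 4800 × 0.50 × 0.30 = 720. That is 720/16 = 45 patients per ward and 720/4 = 180 per arm within each level of randomisation.

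**Expected values.** Let C and T be the uncontaminated control and POD incidences, D = C − T, and k run from 0 (none) to 1 (complete). Hospital-level sites average (C + T)/2 with gap D. All contrasts are ward-level minus hospital-level sites.

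| Mechanism in split hospitals | Control ward | POD ward | Arms averaged | Control v control | POD v POD | Change in control-POD gap |
|---|---|---|---|---|---|---|
| (a) control wards take up POD | C − kD | T | −kD/2 | −kD | 0 | −kD |
| (b) POD wards dilute | C | T + kD | +kD/2 | 0 | +kD | −kD |
| (c) symmetric mixing | C − kD/2 | T + kD/2 | 0 | −kD/2 | +kD/2 | −kD |

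The averaged contrast changes sign with the mechanism and is blind to (c) at every k. The gap contrast is −kD throughout, and the two within-arm contrasts show which mechanism is at work.

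**Numbers.** Control odds 0.29/0.71 = 0.4085; × 0.47 = 0.1920; T = 0.1920/1.1920 = 16.1%; D = 12.9 points. At k = 1 the averaged contrast is −6.4 (a), +6.4 (b) or 0 (c); the gap contrast is −12.9 in all three.

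Range for the averaged contrast under (a) at k = 1, odds ratio 0.47: −2.5 points at C = 10%, −4.7 at 20%, −6.4 at 29%, −9.2 at 64%. With one-third of cases prevented instead (the Abstract's figure) and C = 29%, D = 9.7 and the contrast is −4.8.

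**Baseline differences.** If incidence at the ward-level group of hospitals differs by b for unrelated reasons, the averaged contrast becomes b plus the entry above, and so does each within-arm contrast. In the gap, b cancels if it shifts both arms equally. Chance differences between the POD and the control hospitals within the hospital-level group do not cancel.

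**Precision.** Take C = 29%, mechanism (a), k = 1, 180 patients per cell and a design effect of 1 + 44 × ICC, which is 1 at ICC 0 and 3.2 at ICC 0.05. The gap contrast is a difference of the same four cell means without the averaging, so its standard error is twice that of the averaged contrast.

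| Contrast | Expected size | Standard error | Size/SE |
|---|---|---|---|
| Arms averaged | 6.4 | 2.9 to 5.2 | 2.2 to 1.2 |
| Control v control | 12.9 | 4.4 to 7.8 | 3.0 to 1.7 |
| Change in gap | 12.9 | 5.8 to 10.4 | 2.2 to 1.2 |

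These standard errors allow for clustering by ward only. About two hospitals supply all the uncontaminated control wards, so the real uncertainty is larger.

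**The case against.** The strongest reply is that the article never says the arms are combined. The plural in its reference to incidence rates fits arm-specific rates, per-arm incidence is already planned for the primary analysis, the whole analysis is declared descriptive, and a final statistical analysis plan is promised. Stratifying one descriptive comparison by arm could be detail that a condensed article leaves out. Part of this stands: averaging is the natural reading, not an explicit statement. But the article does more than leave a method open. It states a contrast, between site types, and names no arm where it names one elsewhere. Followed as written, that contrast does not measure what it is said to assess.

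A reader might go further and infer that the comparison is zero whenever contamination is complete. The documents do not support that. They give no direction for contamination, and zero arises only under symmetric mixing. If control wards fully adopt POD, which is a natural worry for an intervention aimed at staff skills and knowledge, the averaged contrast reaches its largest size for that mechanism, D/2.

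A reader might also infer that the comparison would by itself lead to the wrong unit of randomisation in the definitive trial. No decision rule is attached to it: the continuation criteria concern milestone completion and recruitment, and staff movements are to be reported alongside. Those counts show the opportunity for contamination, though, not its effect on delirium.

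Finally, the better contrast is not sharper. Under one-way uptake by control wards, the gap contrast has the same ratio of signal to standard error as the averaged one. That stands, and it limits what the fix can claim.

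**Conclusion.** The point holds as one of identification. Read as written, the contamination comparison averages arms that are balanced 1:1 in both site types. Its expected value is at most half the treatment effect in size, its sign depends on an unspecified mechanism, it is zero under symmetric mixing, and it is confounded with chance differences between two groups of about four hospitals. In the illustration it ranges from −6.4 to +6.4 points under complete contamination, against a constant −12.9 for the change in the control-POD gap.

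The algebra rests on equal ward sizes and 1:1 allocation. The point values rest on an assumed 29% control incidence and an odds ratio of 0.47. If an arm-specific comparison was always intended, the matter reduces to stating it. With eight hospitals, no version of the contrast can settle whether contamination occurred.

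**What to change.** Amend the contamination section, and carry the wording into the statistical analysis plan, so that it states the following:

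- New-onset delirium incidence will be reported by arm within level of randomisation (four cells).
- Control wards will be compared with control wards, and POD wards with POD wards, across the two levels.
- The POD-control contrast will be reported separately for hospital-level and ward-level sites, together with the difference between the two (an arm-by-level term). Confidence intervals will allow for clustering by ward and by hospital.
- These results are descriptive and imprecise, resting on eight hospitals of which only about two are all-control. They will be read with the staff-movement counts already planned for ward-level sites.

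The Trial status section reports recruitment complete and analysis under way. The change needs no new data: it costs one more table and a change of wording. What it buys is a contrast whose meaning does not depend on the direction of contamination, rather than a more precise one.
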